### 3.3.8 Drop-outs and Crossovers

**Drop-outs:** We anticipate that <20% of randomized patients will either not receive the treatment, will not have undergone an index cardiac procedure, or will not consent to remain in the study. The majority will likely be the first reason, in whom coagulation factor replacement will be deemed to be not necessary after it was ordered but before it is administered due to cessation of bleeding or identification of other causes of bleeding. Study sample size has been calculated to compensate for drop-outs.

**Product switching:** Other than the coagulation factor replacement order being cancelled, all patients will be treated according to the randomization schedule on the first and second times when coagulation factor replacement is ordered for the treatment period (24 hours after randomization). Following this, all patients will receive FP when coagulation factor replacement is ordered. To ensure minimal product switching, instructions will be entered into the blood bank information system to dictate the randomization product for the 24 hours after randomization and will flag the laboratory technologists if attempts are made to override the instruction.

### 3.3.9 Outcome Assessments and Independent Data and Safety Monitoring Committee (IDSMC)

An IDSMC will review accumulating safety, endpoint, and other study data (recruitment, retention and compliance, data quality and timeliness, risk vs. benefit). The function of the IDSMC will be to protect and serve the recruited patients particularly pertaining to patient safety as well as to assist and advise the Sponsor on medical questions and issues of study conduct and continuation. The IDSMC will be independent of the investigating team and the Sponsor in operating and formulating recommendations. The IDSMC will review relevant data during the course of the study. The full role of the IDSMC will be detailed in the IDSMC Charter.

## 4 STUDY POPULATION

### 4.1 Population Base

The study will include 120 randomized bleeding adult cardiac surgical patients who require coagulation factor replacement. This should provide 100 evaluable patients, accounting for drop-outs in both arms, with approximately 50 patients assigned to each of the two treatment groups.

#### 4.1.1 Inclusion Criteria

Patients undergoing any index cardiac surgery with or without CPB in whom coagulation factor replacement with PCC or FP is ordered in the operating room for:

1. Management of bleeding, or
2. Anticipated bleeding in a patient who has
  - a) been on-pump for >2 hours, or
  - b) undergone a complex procedure (e.g., aortocoronary bypass [ACB] plus aortic valve replacement).

Coagulation factor deficiency must either be known to exist (as indicated by elevated EXTEM clotting time [CT] or international normalized ratio [INR]) or be suspected based on the clinical situation.

#### 4.1.2 Exclusion Criteria

Patients who meet any of the following criteria are *not* eligible for the study:

1. Undergoing heart transplantation, insertion or removal of ventricular assist devices (not including intra-aortic balloon pump [IABP]), or repair of thoracoabdominal aneurysm
2. Critical state immediately before emergency surgery with high probability of death within 24 hours of surgery (e.g., acute aortic dissection, cardiac arrest 24 hours before surgery)
3. History of heparin induced thrombocytopenia
4. Last preoperative international normalized ratio (INR) >1.5 and patient on warfarin
5. Taken dabigatran, rivaroxaban, apixaban, or edoxaban within 48 hours of start of surgery
6. Taken PCC or plasma within 48 hours before start of surgery
7. History of severe allergic reaction to PCC or plasma
8. Refusal of allogeneic blood products due to religious or other reasons
9. Known pregnancy.

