**Study Procedures:**

When the first order for PCC or FP is received by the blood bank, the technologist will confirm patient eligibility with the clinical team. Following confirmation of eligibility, the technologist will randomize the patient to PCC or FP according to the randomization schedule and prepare and release the product in a tamper sealed container (with weight device in PCC boxes to ensure adequate concealment). The operating room personnel will be blinded to group allocation until the tamper lock seal is broken in the operating room immediately prior to infusion. The rate and route of administration of products will be documented according to current standards.

If a second order is received within 24 hours of randomization, the blood bank technologist will release IMP as determined by the randomization schedule, as per usual practice (a tamper-sealed container will not be used for the second order). For subsequent orders in the operating room and intensive care unit (ICU), the technologist will release FP for both groups.

The type of IMP administered will not be recorded in the chart to ensure that the research personnel assessing outcomes and AEs are blinded to assignment. Patients will also be blinded to treatment allocation.

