PCCs do not contain the full balanced complement of procoagulants and anticoagulants present in FP (51) and it is therefore conceivable that they might be less effective, although *in vitro* studies suggest that PCCs may be more effective than FP in enhancing thrombin generation after cardiac surgery (46). Also, because PCCs contain more procoagulants than anticoagulants, they may carry a higher risk of thrombotic events, disseminated intravascular coagulation and acute kidney injury (47, 52–56). Finally, since PCCs contain heparin, they are contraindicated in patients who are allergic to heparin or have a prior history of heparin induced thrombocytopenia.

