### 3.3.7 Blinding of Investigational Medicinal Product

Given that the products have quite different physical properties, it is not possible to blind treating clinicians to group assignment. To minimize bias, treating clinicians will be blinded to group assignment until immediately prior to IMP infusion. The blood bank technologist will randomize the patient to PCC or FP, according to the randomization schedule, and prepare and release the product in a tamper sealed container (with weight device in PCC boxes to ensure adequate concealment). The operating room personnel will be blinded to group allocation until the tamper lock seal is broken in the operating room immediately prior to infusion. For the second order, a tamper-sealed container will not be used and the blood bank technologist will release IMP as determined by the randomization schedule, as per usual practice. The type of IMP administered will not be recorded in the chart to ensure that the research personnel assessing outcomes and AEs are blinded to assignment. Patients will also be blinded to treatment allocation.

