#### **4.2.2 Forbidden Concomitant Therapy**

No concomitant therapies are forbidden, except for the use of PCCs other than *Octaplex* (unless unavailable in emergency situations).

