## 6.1 Study Procedure

### 6.1.1 Prior to Enrolment

#### **First coagulation factor replacement order from the surgical team received at the blood bank**

The blood bank technologist will confirm the following:

- Eligibility criteria are met
- Coagulation measures (coagulation profile) are available or have been collected or will be collected before the IMP is infused

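### Heparin allergy is named as a contraindication to PCC in section 1.1 but is missing from the exclusion criteria, so such a patient can be randomised to PCC.

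*Combined protocol and SAP*

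**What the plan says.** The Prothrombin Complex Concentrate part of protocol section 1.1 explains that PCCs contain heparin, so that "they are contraindicated in patients who are allergic to heparin or have a prior history of heparin induced thrombocytopenia". Table 2 in section 5.1.1 confirms this for Octaplex: 80–310 IU of heparin per 20-mL vial and 160–620 IU per 40-mL vial.

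Exclusion 3 reads "History of heparin induced thrombocytopenia" in section 4.1.2, and the Study Outline has the same wording. The only allergy exclusion is number 7, in section 4.1.2 "History of severe allergic reaction to PCC or plasma"; the Study Outline says FP in place of plasma.

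Before randomisation, section 6.1.1 has the blood bank technologist check that "Eligibility criteria are met". The Study Outline adds that "the technologist will confirm patient eligibility with the clinical team". Under section 3.3.7, operating room staff are "blinded to group allocation until the tamper lock seal is broken in the operating room" just before the first infusion.

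**The concern.** The protocol states two contraindications and turns only one into an exclusion. A patient who is allergic to heparin, has no history of HIT and has never reacted to PCC or plasma meets no exclusion.

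Two things could follow. The patient could be given a product that the protocol says should not be given. Or the clinical team could notice only on opening the sealed container, when the patient is already randomised. In routine practice at these sites the cardiac anesthesiologist chooses between PCC and FP (section 3.3.2) and could simply choose FP. Randomisation removes that choice.

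Enrolment also precedes consent. Section 10.3 defends this partly on the ground that nothing suggests participation puts patients at risk. Allocating someone to a contraindicated product does not fit that argument.

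**Working it through.** The plan gives no figure to reproduce. The main check is a comparison of texts.

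**1. Contraindications against exclusions**

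| Contraindication in section 1.1 | Exclusion 3 (both lists) | Exclusion 7 (both lists) |
|---|---|---|
| Prior HIT | Covered | Not addressed |
| Heparin allergy | Not covered | Not covered: PCC or plasma/FP only |

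**2. Other places that might screen for it**

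- Section 4.1.1 (inclusion) admits any index cardiac surgery, with or without bypass, and does not mention heparin.
- Section 4.2.2: "No concomitant therapies are forbidden, except for the use of PCCs other than" Octaplex. This does not restrict Octaplex itself.
- Section 6.1.1 refers back to the eligibility criteria, so it inherits the gap.
- The Study Outline's conversation with the clinical team concerns the same criteria.
- Section 3.3.7 lets clinicians see the product, but only after randomisation.

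None of these names heparin allergy.

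**3. What happens after randomisation**

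Section 3.3.8 says: "Other than the coagulation factor replacement order being cancelled, all patients will be treated according to the randomization schedule". Section 4.3.1 lets the investigator withdraw a patient. The protocol gives no explicit route for switching a contraindicated patient to FP. Under section 9.2, a patient who receives no IMP leaves the ITT set. An allergic patient allocated to FP would be treated and stay in, so any loss would fall on the PCC arm alone.

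**4. Heparin given with PCC**

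From Table 2, one 20-mL vial contains 500 IU of factor IX and 80–310 IU of heparin.

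- 1500 IU dose, 3 vials: 3 × 80 = 240 to 3 × 310 = 930 IU of heparin.
- 2000 IU dose, 4 vials: 4 × 80 = 320 to 4 × 310 = 1240 IU.
- Two 2000 IU doses, the most PCC that the randomised regimen allows: 640 to 2480 IU.

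**5. Number of patients**

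The documents give no prevalence of heparin allergy. Assume a proportion p of 0.001 to 0.005 among otherwise eligible patients. The plan randomises 120, about 60 per arm.

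| Quantity | Formula | p = 0.001 | p = 0.005 |
|---|---|---|---|
| Expected among all randomised | 120p | 0.12 | 0.60 |
| Expected in the PCC arm | 60p | 0.06 | 0.30 |
| Chance of at least one in the PCC arm | 1 − (1 − p)^60 | 0.0583 | 0.2597 |

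The last row is the chance that at least one patient with a recorded allergy is allocated to PCC. It is not the chance of an infusion or a reaction.

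**The case against.** The strongest reply is that general safeguards make the gap mostly theoretical.

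- Orders must accord with accepted clinical standards (section 3.2).
- The products go only to patients in whom the ordering physician considers them indicated (section 3.3.2).
- Investigators receive the Product Monograph (section 8.2).
- The clinical team is consulted on eligibility and sees the product before infusing it.
- Enrolment happens in the operating room after surgery has started. Most patients will already have had heparin: section 1.1 describes its use in bypass, and section 4.2.1 expects the dose to be recorded.
- One untreated patient is well within the drop-out allowance of under 20% in section 3.3.8.

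Much of this stands. It lowers the number exposed to a real hazard below the counts above, by an amount the documents do not allow one to estimate, and it confirms that inference is unaffected.

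It does not close the gap. Sections 3.2 and 3.3.2 ask whether factor replacement is warranted, and the Monograph is background information; none of these screens for heparin allergy. Prior heparin exposure would argue equally against the HIT exclusion, which was kept. The patient who matters most is one from whom heparin was withheld because of a known allergy. Seeing the product at the bedside comes after randomisation, and section 1.1 notes that FP needs compatibility matching and thawing, so a late change costs time in a bleeding patient.

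**Conclusion.** The concern holds. Section 1.1 and the exclusion lists disagree, and the eligibility rule admits a patient whom the protocol regards as contraindicated for one of the two arms. Confidence in the wording gap is high. The practical hazard is small and less certain: it rests on an assumed prevalence of 0.1% to 0.5% and is reduced further by clinician checks and prior heparin exposure. Endpoints, sample size and analysis are not materially affected. The correction should be made because it concerns a stated contraindication, allocation precedes consent, and the change is nearly free.

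**What to change.** Reword exclusion 3 in the Study Outline and in section 4.1.2 to cover known allergy to heparin or a history of HIT. Naming heparin allergy in the section 6.1.1 blood bank check as well is not strictly needed, since that check already refers to the criteria, but it is a useful prompt.

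SAP version 2.0 follows a Blinded Data Review Meeting, so pilot enrolment may be over. The change still matters then, because the pilot is meant to inform the Phase 3 design and the list could be copied forward uncorrected. The amended wording should go into the Phase 3 protocol.

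The cost is one line in each of two lists, an optional line in the blood bank check and, on the assumed range, 0.12 to 0.60 patients per 120 randomised. The planned sample size does not change.

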### 4.2 Prior and Concomitant Therapy

Details on medications taken within 1 week before enrolment and any concomitant medications taken during the study must be recorded in the case report form (CRF).

#### 4.2.1 Permitted Concomitant Therapy

Participating hospitals will use a standardized point-of-care based transfusion algorithm that will employ a targeted approach to correct coagulopathy (as per the validated TACS algorithm) (4), but with selection of PCC or FP determined according to the patient's assigned grouping and using the doses described in **Section**

**3.3.2.** Recommended RBC transfusion thresholds will be 75 g/L during surgery and 85 g/L in bleeding or unstable patients.

Concomitant administration of any therapies required as part of standard patient care is permitted but must be recorded in the CRFs. All hemostatic drugs or products administered (e.g., heparin and protamine dose, anti-fibrinolytic drugs, desmopressin, rFVIIa, idarucizumab, andexanet alpha, or topical hemostatic agents) will be recorded, as well as all procedures that may influence amount of bleeding (e.g., retrograde autologous priming of CPB circuit, cell salvage). In addition, concomitant medications used to treat SAEs will be reported throughout the duration of follow-up (up to POD-28).

#### **4.2.2 Forbidden Concomitant Therapy**

No concomitant therapies are forbidden, except for the use of PCCs other than *Octaplex* (unless unavailable in emergency situations).

### **4.3 Withdrawal and Replacement of Patients**

#### **4.3.1 Premature Patient Withdrawal**

Patients have the right to withdraw from the study at any time for any reason, without the need to justify their decision. The Investigator also has the right to withdraw patients for reasons such as intervention no longer indicated due to stoppage of bleeding, randomization of ineligible patients, and adverse events attributed to previous doses of IMP. For any withdrawals after study entry, the Investigator will obtain all the required details and document the reason(s) for discontinuation, and report to the IDSMB and REB where indicated. If the reason for withdrawal of a patient is an AE, the main specific event or laboratory test will be recorded, and the Investigator will make thorough efforts to clearly document the outcome.

#### **4.3.2 Patient Replacement Policy**

Patients withdrawn from the study for safety reasons will not be replaced.

### **4.4 Assignment of Patients to Treatment Groups**

Patients will be assigned to treatment with either PCC or FP using a permuted-block, stratified (by centre) random allocation scheme prepared by a biostatistician not involved in the conduct of the trial. Group allocation will apply to the first two doses of IMP during the treatment period (up to 24 hours from randomization). For any additional doses (i.e., the third dose and thereafter), patients in both groups will receive FP. Subjects/patients are not permitted to re-enroll in the study.

### **4.5 Relevant Protocol Deviations**

In the case of any major protocol deviation, the Investigator (Sponsor) will decide on the further participation of the patient in this study.

### **4.6 Subsequent Therapy**

Any subsequent hemostatic therapy will be according to institutional standard of care.

## 5 INVESTIGATIONAL MEDICINAL PRODUCTS

### 5.1 Characterization of Investigational Products

#### 5.1.1 Octaplex

*Octaplex* is a product derived from human plasma containing the coagulation factors II, VII, IX, and X and proteins C and S. It is manufactured by chromatographic purification of cryoprecipitate-poor plasma.

The *Octaplex* manufacturing process includes two dedicated virus inactivation/removal steps, by way of a solvent/detergent viral inactivation process and a virus removal nanofiltration step. The solvent/detergent treatment causes enveloped viruses such as pseudorabies virus (PRV), Schmallenberg virus (SBV), and human immunodeficiency virus [HIV] type 1 to be irreversibly destroyed. Nanofiltration removes infectious agents from protein solutions on the basis of their size may be the only method to date permitting efficient removal of enveloped (e.g., HIV-1, SBV, PRV, bovine viral diarrhea virus) and non-enveloped viruses (e.g., hepatitis A virus) under conditions where 90–95% of protein activity is recovered (79). Other precautions against viral transmission include: selection of plasma donors, screening of donations and plasma pool, as well as quality control measurements of the final product.

#### Composition of Octaplex

*Octaplex* is a human PCC for intravenous (IV) use. Its ingredients are listed in **Table 2**.

**Table 2** Composition of *Octaplex*

| Ingredients                                          | Quantity per 20-mL vial | Quantity per 40-mL vial |
|------------------------------------------------------|-------------------------|-------------------------|
| Active substances                             |                         |                         |
| Human coagulation factor II                          | 280–760 IU              | 560–1520 IU             |
| Human coagulation factor VII                         | 180–480 IU              | 360–960 IU              |
| Human coagulation factor IX                          | 500 IU                  | 1000 IU                 |
| Human coagulation factor X                           | 360–600 IU              | 720–1200 IU             |
| Further active ingredients                    |                         |                         |
| Protein C                                            | 260–620 IU              | 520–1240 IU             |
| Protein S                                            | 240–640 IU              | 480–1280 IU             |
| Clinically relevant non-medicinal ingredients |                         |                         |
| Heparin                                              | 80–310 IU               | 160–620 IU              |
| Sodium citrate                                       | 17.0–27.0 mmol/L        | 17.0–27.0 mmol/L        |

IU, international units

Further excipient: Solvent (Water for Injection)

Small amounts of the S/D reagents TNBP (5 µg/ml) and Polysorbate 80 (50 µg/mL) may remain in the finished product. These substances are added during the manufacturing process because of their capacity to inactivate lipid-enveloped viruses.

**Conditions for Storage and Use**

The IMP has to be stored at room temperature (not more than 25°C) and protected from light. The product must not be frozen. The Investigator/authorized personnel at the site will ensure that the IMP is stored in appropriate conditions with restricted access and in compliance with national regulations.

**Dose and Dosing Schedule**

Patients randomized to *Octaplex* will receive 1500 IU for IBW≤60 kg or 2000 IU for IBW>60 kg (corresponding to weight-base dosing range of 20–25 IU/kgIBW rounded up to nearest 500 IU increment, up to a maximum of 2000 IU per dose) the first and second occasions when coagulation factor supplementation is ordered during the first 24 hours after randomization. If an order for a second dose is received, the second dose of *Octaplex* or FP will be released and administered to patients according to the randomized group allocation as per the first dose. For any additional doses (i.e., the third dose and thereafter), patients in both groups will receive FP (in 1 U increments at the discretion of the ordering physician).

| Patient weight | Octaplex dose | Plasma dose |
|----------------|---------------|-------------|
| ≤60 kg         | 1500 IU       | 3 U         |
| >60 kg         | 2000 IU       | 4 U         |

**Preparation**

Each vial of *Octaplex* will be reconstituted with 20 mL or 40 mL WFI (as per the manufacturer's instructions) at room temperature (not more than 25°C). *Octaplex* dissolves at room temperature to an almost colorless and slightly opalescent solution within 10 minutes. It will not be used if it remains cloudy or contains particulates.

**Method of Administration**

*Octaplex* will be administered intravenously, immediately after reconstitution as recommended, via free-flowing IV syringe injection. *Octaplex* should not be mixed with other medicinal products or crystalloid intravenous solutions.

**Packaging and Labeling**

Commercial supplies of *Octaplex* will be used. Several batches of IMP may be used throughout the study. The batch numbers will be recorded in the CRFs and reported in the final study report.

**5.1.2 Frozen Plasma**

Patients randomized to FP will receive 3 U for IBW≤60 kg or 4 U for IBW>60 kg (corresponding to weight-base dosing range of 10–15 mL/kgIBW rounded up to 1 U increment, up to a maximum of 4 U per dose) for each order during the first 24 hours after randomization. FP will be provided by the Canadian Blood Services and will be stored, thawed, and pooled by the blood bank according to current standards. FP will be infused as per standard hospital protocols at the participating institutions (i.e., infused using timing recommended in the current monograph through standard 140 µm blood infusing set).

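### Section 5.1.2 and the blood bank instruction in section 3.3.8 do not match the rule stated elsewhere for third and later orders within 24 hours, so plasma issued per order can differ between arms by up to 2 or 3 U

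*Combined protocol and SAP*

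**What the plan says.** Section 5.1.2 sets the dosing for the FP arm: "Patients randomized to FP will receive 3 U for IBW≤60 kg or 4 U for IBW>60 kg", applied "for each order during the first 24 hours after randomization". Nothing in that section confines the fixed amount to the first two orders.

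The parallel text for Octaplex (5.1.1, Dose and Dosing Schedule) does set such a limit. It ties the fixed dose to the first and second occasions and then says of later doses that "patients in both groups will receive FP (in 1 U increments at the discretion of the ordering physician". The same rule with the same step size stands in the synopsis (Study Design; Test Product, Dose, and Mode of Administration), in protocol 3.2, 3.3.2 and 6, and in SAP 1.2. Section 4.4 agrees on the product without naming an amount: "Group allocation will apply to the first two doses of IMP during the treatment period", with FP for everyone afterwards. So does the synopsis under Study Procedures, where for later orders "the technologist will release FP for both groups".

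Section 3.3.8 gives two messages in one paragraph. It says that allocation governs the first two orders and that all patients get FP after that. Its last sentence then describes entries in the blood bank's computer that "dictate the randomization product for the 24 hours after randomization and will flag the laboratory technologists if attempts are made to override the instruction".

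The amounts feed P2 (a primary endpoint) and S3, which count allogeneic products by type and in total. In SAP 6.1 the total includes FP. SAP 4.6 repeats the analysis on an adjusted total without FP.

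**The concern.** These are operating instructions. A blood bank that writes its FP-arm procedure from the FP section finds a fixed 3 or 4 U and no two-order limit. One that works from 5.1.1 or section 6 finds 1 U steps in both arms. The system instruction in 3.3.8 is the protocol's stated safeguard against product switching. As described, it runs by time only, so a release that obeys the two-order rule for a PCC patient would set off the flag.

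At stake is whether plasma quantity at third and later orders reflects bleeding or the release rule. Section 1.2 says the pilot results will be used to size the Phase 3 trial, so a rule-driven part of the plasma difference could carry into that calculation.

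**Working it through.** The plan gives no figure to reproduce here, and the sample size was set on pragmatic grounds, so nothing below depends on a power calculation.

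**1. The texts side by side, for a third or later order within 24 h of randomization**

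| Place | FP arm | PCC arm |
|---|---|---|
| 5.1.2 | 3 U (IBW ≤60 kg) or 4 U (IBW >60 kg) | not addressed |
| Synopsis (two places), 3.2, 3.3.2, 5.1.1, 6, SAP 1.2 | FP in 1 U steps, physician decides | the same |
| 4.4; synopsis, Study Procedures | FP, no amount | FP, no amount |
| 3.3.8, statement on orders | FP, no amount | FP, no amount |
| 3.3.8, system instruction | FP | randomised product is dictated; an FP release is the flagged action |

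No text gives one section precedence over another.

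**2. Gap per order.** Read 5.1.2 literally for the FP arm and apply the 1 U rule to the PCC arm. Let d be the fixed FP amount and k the amount the physician orders in the PCC arm, with k from 1 to d. The gap is d − k.

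- IBW ≤60 kg: d = 3, so the gap is 2, 1 or 0 U.
- IBW >60 kg: d = 4, so the gap is 3, 2, 1 or 0 U.

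Under one common rule for both arms the rule-driven gap is 0 U.

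**3. In the SAP's counting units.** SAP 6.2 counts a non-apheresis FP unit as 1 and an apheresis unit as 2, and treats unknown status as apheresis. The maximum gap of 2 to 3 U is therefore 2 to 3 allogeneic units (non-apheresis) or 4 to 6 (apheresis or unknown).

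**4. Shift in the arm mean.** Shift = q × maximum gap, where q is the share of patients with one such order. The documents do not give q; the values here are assumptions.

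| q (assumed) | IBW ≤60 kg (2 U) | IBW >60 kg (3 U) |
|---|---|---|
| 5% | 0.10 U | 0.15 U |
| 10% | 0.20 U | 0.30 U |
| 20% | 0.40 U | 0.60 U |

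Counted as apheresis units these double, to a range of 0.2 to 1.2. If physicians order comparable amounts in the PCC arm, the shift is zero.

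**5. Comparison with the designed difference.** Two full orders already give the FP arm 2 × 3 = 6 U or 2 × 4 = 8 U of plasma as study product, against 0 U in the PCC arm. At the maximum gap, a third order takes the difference to 6 + 2 = 8 U or 8 + 3 = 11 U.

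**6. Endpoints reached.** The FP component and the cumulative sum in P2 and S3 are affected. The adjusted sum contains only red cells and platelets, so the issue cannot enter it.

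**The case against.** The strongest reply is that the intended rule is plain. The 1 U rule for both groups is stated repeatedly, including in the section directly before 5.1.2. Section 5.1.2 never mentions a third dose, and 3.3.2 opens in a similarly unrestricted way before stating the two-order limit. On this view 5.1.2 has merely lost a qualifier. That is plausible and limits how serious the point is. It does not remove the conflict, because 5.1.2 is the section that defines FP dosing.

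Four stronger readings are tempting, and the documents do not support them:

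- **The PCC arm gets only 1 U per later order.** The text sets a step size and leaves the amount to the physician, who may order 3 or 4 U. The arms can differ; they need not.
- **PCC patients would receive a third dose of Octaplex.** For IBW >60 kg that would be 3 × 2000 = 6000 IU against 2 × 2000 = 4000 IU. It requires reading the system sentence in 3.3.8 against the two sentences before it, and against 4.4, 5.1.1 and the other sections. The system is said to flag overrides, not to block them, and no text provides for a third PCC dose.
- **Section 4.2.2 adds to the conflict.** It says "No concomitant therapies are forbidden, except for the use of PCCs other than" Octaplex. That concerns concomitant therapy and is silent on third-order release; silence is not a contradiction.
- **P2 as a whole is compromised.** Plasma in P2 already differs by design through orders 1 and 2, and the FP-excluded sum is planned alongside.

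**Conclusion.** The inconsistency is real and affects operating rules, so it is more than clerical. It has two parts: the unlimited wording in 5.1.2, and a time-only system instruction in 3.3.8 that does not fit the two-order rule in the same paragraph.

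The effect on the analysis is modest and conditional. It arises only if 5.1.2 is followed literally for the FP arm and PCC-arm physicians order less than the fixed amount. The per-patient shift also rests on the assumed third-order rate and on one such order per patient. A PCC patient given 1 U may have further orders, which would narrow the cumulative gap. The point should be corrected; it does not undermine the trial's main comparisons.

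**What to change.** Reconcile 5.1.2 and the system-instruction sentence in 3.3.8 with the synopsis, protocol 3.2, 3.3.2, 4.4, 5.1.1 and 6, and SAP 1.2, so that the documents state one rule for third and later orders. Set the blood bank instruction to match that rule by order number as well as by time. Which release rule is right is for the sponsor to decide.

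Optionally, add a line to SAP 4.6 to report plasma from third and later orders separately, in units by arm. Section 6.1.2 already collects the number and timing of transfusions for the 24 hours after randomization. No change to S1 is needed.

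The cost is protocol wording in two places, one change to the blood bank instruction and, if wanted, one SAP line. No new data are required. If recruitment has ended by the time this is acted on, the study report should state which rule each blood bank applied.
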